### Sample Size Considerations

The primary objective of this study is the measurement of changes in body weight and waist circumference. Based on a recent study by Haste et al, which evaluated a web-based weight loss intervention among men with diabetes, we expect a weight loss of at least 4.5 kg at 12 months in the intervention group as compared with 2.5 kg in the control group [8] (Textbox 2).

Sample size calculation.A power calculation based on standard deviations observed in the study [8] shows that the detection of a difference in weight loss of 2.0 kg with a power of 0.95% requires 55 participants in the intervention group and 32 in the control group. To allow for drop out according to the experienced attrition rates in the same study [8] (39% of participants in the intervention group and 57% in the control group are expected to drop out at 12 months), we will recruit 100 participants in the intervention group and 70 in the control group (Figure 1). To be able to stratify analyses according to obese participants at risk of developing chronic diseases and obese participants with diabetes, we will recruit 100 obese participants at risk of developing chronic diseases and 100 obese participants with diabetes. Therefore, in total, we will consider 200 participants in the intervention group and 140 in the control group.

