### Analysis Strategy

All data are analyzed according to the intention-to-treat principle [43]. Analyses are mainly carried out according to the two target groups. However, stratification according to participant characteristics and user experiences is applied to investigate associations between success and the different characteristics. Ordinary least square regression and difference between groups over time are used to explore significant associations. Statistical significance is inferred at a two-tailed *P* value <.05. Robust standard errors are calculated. Data are analyzed by experts in biostatistics. After the study, all data will be made accessible on request in anonymized form to allow full peer scrutiny and facilitate secondary research.

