## Results

### Progress

From March 2018 to March 2019, 799 potential participants were evaluated for participation. A total of 340 met the inclusion criteria, consented to participate, filled out the web-based questionnaire, and were randomized into study groups. Among participants with type 2 diabetes, 100 (49 female participants) were randomized to the intervention group and 70 (32 female participants) were randomized to the standard care group. Among overweight participants, 100 (81 female participants) were randomized to the intervention group and 70 (52 female participants) were randomized to the standard care group.

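### The sample-size paragraph prints an impossible power (0.95%), and its drop-out rates leave about 30 control completers per target group against the 32 it requires; the effect on power is negligible

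*Protocol article*

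**What the plan says.** All the sample-size figures stand in the Sample Size Considerations section of the protocol article, including its sample-size textbox.

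- Effect, a difference of 2.0 kg between the arms: "we expect a weight loss of at least 4.5 kg at 12 months in the intervention group as compared with 2.5 kg in the control".
- Variability: "A power calculation based on standard deviations observed in the study [8"]. No value is printed, and the word is in the plural.
- Power and evaluable numbers: the calculation is done "with a power of 0.95% requires 55 participants in the intervention group and 32 in the control group".
- Drop-out, taken from the same cited study: "39% of participants in the intervention group and 57% in the control group are expected to drop out at 12 months".
- Recruitment meant to absorb that drop-out: "we will recruit 100 participants in the intervention group and 70 in the control group". This is doubled to cover the two target groups, giving 200 and 140.

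The significance level is in Analysis Strategy: "Statistical significance is inferred at a two-tailed *P* value <.05". The Progress section reports that 100 and 70 were in fact randomized in each target group.

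**The concern.** The paragraph is the article's only statement of power, and it sizes each target group separately so that the analyses can be stratified. Two of its figures conflict with others in the article.

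The printed power is smaller than the significance level, so read literally it describes no possible two-sided test. The number of controls recruited, after the stated drop-out, falls below the number of controls stated as required. The requirement, the drop-out rate and the recruitment figure cannot all hold for the control arm.

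At stake is whether a reader can rely on the claimed power within each target group, and whether the trial was set up to miss its own target. The first needs a correction to the text. The second needs a calculation before anyone calls it a loss of power.

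**Working it through.** **Inputs.** From Sample Size Considerations: difference 2.0 kg; required evaluable 55 and 32; drop-out 39% and 57%; recruited 100 and 70 per target group. From Analysis Strategy: two-sided 5%. The SDs are not given.

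**1. The printed power.** The power of a two-sided 5% test is lowest when there is no difference, and there it equals 5%. Since 0.95% is below 5%, no effect and no SD can produce it. Reading it as 0.95 gives a conventional value and needs only the percent sign removed.

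**2. Can 55/32 be reproduced?** Not directly, because no SD is printed. It can be solved backwards, assuming one common SD and 95% power (normal approximation):

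SD = 2.0 / [(1.960 + 1.645) × √(1/55 + 1/32)] = 2.0 / (3.605 × 0.2223) = 2.50 kg.

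The noncentral t version gives 2.47 kg. So 55/32 is attainable, but this SD is inferred and is not a figure in the article.

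**3. Drop-out applied to the recruited numbers.**

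| Arm, per target group | Recruited | Retained | Expected completers | Required | Met? | Recruits needed |
|---|---|---|---|---|---|---|
| Intervention | 100 | 0.61 | 61.0 | 55 | yes, +6 | 55/0.61 = 90.2, so 91 |
| Control | 70 | 0.43 | 30.1 | 32 | no, −2 | 32/0.43 = 74.4, so 75 |

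Over both target groups, the controls needed are 2 × 75 = 150 against 140 planned. Pooled expected completers are 122 and about 60.

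**4. What the shortfall costs.** With a common SD, precision depends on √(1/n₁ + 1/n₂):

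- 55/32: 0.2223
- 61/30: 0.2230

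The two are almost equal, because six extra intervention completers offset two missing controls. Power for 2.0 kg, two-sided 5%:

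| SD assumption (intervention / control) | Method | 55/32 | 61/30 |
|---|---|---|---|
| Common 2.47 kg | noncentral t | 95.0% | 94.9% |
| Common 2.5 kg | normal approximation | 94.9% | 94.8% |
| 3.2 / 2.0 kg | normal approximation | 94.8% | 95.4% |
| 1.8 / 2.82 kg | normal approximation | 95.0% | 94.4% |

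The unequal pairs are assumed values, chosen because they also give about 95% at 55/32. Across these cases, power at 61/30 lies between 94.4% and 95.4%. Pooled over both target groups (122/60), it is 99.9% at a common SD of 2.47 kg.

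**The case against.** The strongest reply is that this is editorial. The power is an obvious misprint, two missing controls change power by about a tenth of a percentage point under a common SD, and with some unequal SDs power even rises. A condensed article may leave the SD to the full protocol. The analysis is by intention to treat, and the section on prevention of drop-out says that participants excluded early will be asked for final measurements, so 30 is a planning expectation and not necessarily the number analysed. Most of this stands, and it is why the point is minor. It does not remove the two errors, since no other part of the article corrects the power or reconciles 70 controls with 32 completers at 57% drop-out.

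A reader might be tempted to go further in three ways, none supported by the article.

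- **That 55/32 works only with an SD of about 2.5 kg.** The text speaks of SDs in the plural, and unequal pairs such as 3.2 and 2.0 kg fit as well.
- **That each target group is badly underpowered.** At a common SD of 4, 5 or 6 kg, power at 61/30 would be 60%, 43% or 32%, but those SDs appear nowhere in the article. A missing SD makes the calculation uncheckable here; it does not show it to be wrong.
- **That SDs from men with diabetes cannot serve the group without diabetes.** In that group 81 + 52 = 133 of 170 are women ("Among overweight participants, 100 (81 female participants) were randomized to the intervention group and 70 (52 female participants"), but nothing in the article says that the SD of weight change differs by sex or diabetes status.

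**Conclusion.** The point holds as two errors of statement, both of minor severity. The power of 0.95% is impossible under the article's own two-sided 5% level. The control arm's expected completers, about 30 per target group, fall two short of the stated 32; recruitment is 70 against the 75 needed.

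Neither shows that the design is weaker than intended. If 95% power was meant, power at the expected completers stays close to 95% under a common SD near 2.5 kg and under the unequal pairs tried. This rests on the stated drop-out rates, on the 2.0 kg difference, and on the SDs used being such that 55/32 does give 95% power. The article does not show which SDs those were, so that last condition cannot be confirmed from it.

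**What to change.** Correct one paragraph in Sample Size Considerations:

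- Replace 0.95% with the intended power.
- State that 100 and 70 recruited per target group are expected to give 61 and 30 completers (122 and 60 pooled), and acknowledge that 32 controls would have needed 75 recruits per target group.
- Print the SD or SDs taken from the cited study, and restate the power at 61/30 and 122/60 with them.

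Recruitment is complete at the planned numbers, so no participants should be added, and nothing in the analysis changes. The cost is a few sentences and one recalculation from values the authors already hold.

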### Prevention of Drop Out and Loss to Follow-Up

Based on prior experience, approximately 15% of participants will drop out during the first 2 weeks owing to technological challenges, etc. Likewise, after 3 months, approximately 20% of participants will lose motivation and be less active on the platform [8]. The coach will endeavor to maintain participation through phone calls, text messages, and, if necessary, face-to-face meetings. In the case of exclusion before the end of the trial (eg, due to pregnancy), the participant will be asked to complete a final questionnaire and have objective parameters measured in order to provide data for the intention-to-treat analysis.

## Results

### Progress

From March 2018 to March 2019, 799 potential participants were evaluated for participation. A total of 340 met the inclusion criteria, consented to participate, filled out the web-based questionnaire, and were randomized into study groups. Among participants with type 2 diabetes, 100 (49 female participants) were randomized to the intervention group and 70 (32 female participants) were randomized to the standard care group. Among overweight participants, 100 (81 female participants) were randomized to the intervention group and 70 (52 female participants) were randomized to the standard care group.

### Findings

The hypothesis is that the intervention group will demonstrate decreased body weight and a much higher percentage of patients with normalization of their HbA_1c_ levels as compared with the control group. A relevant percentage of participants in the intervention group are expected to decrease their use of glucose-lowering medications and improve their QoL much more as compared with the control group. Operational costs are expected to be lower than standard care and the intervention is expected to be cost-effective for the intervention group.

### Timeline

The first baseline assessments were carried out in March 2018. The trial has now reached the 12-month follow-up period for all included participants, and results are expected by the middle of 2020. The 2-year follow-up will be carried out between March 2020 and April 2021.

## Discussion

This is the first time an app and web-based eHealth lifestyle coaching program implemented in Danish municipalities will be clinically and economically evaluated in a strong scientific setup. The study is expected to show that human support through a digital lifestyle intervention program leads to relevant weight loss as compared with a control group receiving standard care, and more importantly, the study is expected to show that digital lifestyle support results in more than twice as many patients with type 2 diabetes reaching a relevant weight loss of 3% to 5% or more [8]. These results are expected to be clinically relevant for patients with type 2 diabetes when weight loss is sustained for more than 2 years [44]. Moreover, these findings will support that the remission rates of patients with type 2 diabetes can be improved by the use of digital lifestyle coaching at a level comparable to other more intensive resource-heavy strategies [5,7]. If the LIVA 2.0 eHealth lifestyle coaching program is proven to be effective, there is a great potential for decreasing obesity rates and rehabilitating patients with type 2 diabetes and other related chronic diseases cost-effectively though human digital lifestyle coaching.

## Appendix

Multimedia Appendix 1 YouTube video showing an example of the LIVA app used in real life.

Multimedia Appendix 2 Included variables, definitions, categories, and source.

## Abbreviations

BCT: behavior change technique
DKK: Danish Krones
HbA_1c_: hemoglobin A_1c_
LIVA: long-term Lifestyle change InterVention and eHealth Application
QOL: quality of life
RCT: randomized controlled trial
SF-12: 12-item Short Form Survey
SMART model: specific, measurable, attainable, relevant, timely
